# SYNOPSIS

| **Long Study Title** | Association of changes in disease activity and changes in patient-reported quality of life in non-alcoholic steatohepatitis | |
| --- | --- | --- |
| **Short Study Title** | Disease activity and quality of life in non-alcoholic steatohepatitis | |
| **Nature of Study Participants** | Adults diagnosed with non-alcoholic steatohepatitis who participated in previous clinical trials and agreed for data to be shared | |
| **Intended number of participants** | 422 | |
| **Planned Study Period** | February 2021 – May 2021 | |
|  | **Objectives** | **Outcome Measures** |
| **Primary** | **Primary objectives**  To examine the association between changes in disease activity (fibrosis score) and changes in   1. Physical functioning 2. Physical role 3. Pain 4. General health 5. Fatigue 6. Social function 7. Emotional role 8. Emotional well-being | Univariable and multivariable regression coefficients between changes in disease activity (fibrosis score) and changes in   1. Physical functioning 2. Physical role 3. Pain 4. General health 5. Fatigue 6. Social function 7. Emotional role 8. Emotional well-being |
| **Secondary** | **Secondary objectives**   1. Repeat the primary analysis with the NAFLD activity score as a measure of disease activity 2. To examine the association between changes in disease activity (fibrosis and the NAFLD activity score) and changes in 3. SF-36 physical component 4. SF-36 mental component | 1. Univariable and multivariable regression coefficients between changes in disease activity (as NAFLD activity score) and changes in 2. Physical functioning 3. Physical role 4. Pain 5. General health 6. Fatigue 7. Social function 8. Emotional role 9. Emotional well-being 10. Univariable and multivariable regression coefficients between changes in disease activity (fibrosis and the NAFLD activity score) and changes in 11. SF-36 physical component 12. SF-36 mental component |

# ABBREVIATIONS

| CUREC | Central University Research Ethics Committee |
| --- | --- |
| FLINT | Farnesoid X nuclear receptor ligand obeticholic acid for non-cirrhotic, non-alcoholic steatohepatitis |
| MS IDREC | Medical Sciences Interdivisional Research Ethics Committee |
| NAS | Non-alcoholic fatty liver disease activity score |
| NASH | Non-alcoholic steatohepatitis |
| NIDDK | National Institute of Diabetes and Digestive and Kidney Diseases |
| PIVENS | Pioglitazone versus Vitamin E versus Placebo for the Treatment of Nondiabetic Patients with Non-alcoholic Steatohepatitis |
| PI | Principal Investigator |

# BACKGROUND AND RATIONALE

There have been numerous trials looking at pharmacological options for managing non-alcoholic steatohepatitis (NASH) with modest effects.^1 2^ Yet to date, none of these drugs have been licensed for treatment in Europe and the USA. NASH is strongly associated with obesity, and considered to be the hepatic component of the metabolic syndrome.^3^ NASH is associated with various degrees of hepatic fibrosis, which is the strongest predictor for long-term liver morbidity and mortality. Recent studies have suggested that weight loss is associated with improvements in histological features of NASH and fibrosis,^4^ and intensive weight loss with behavioural support may be an effective treatment option for this group of patients.

Measures of patient-reported health-related quality of life (HRQoL) scores are important parts of decision-making when considering approvals of future treatment options. A recent literature review found that patients with NASH had an impaired HRQoL, compared with the general population, and with NAFLD patients.^5^ Those with NASH-related cirrhosis (i.e. advanced fibrosis) have poorer HRQoL scores than those with non-cirrhotic NASH.^6^ Patients were found to experience a broad range of physical and mental symptoms, especially fatigue, abdominal symptoms, and worry.^5 7^ Typically disease activity is negatively associated with HRQoL in cross-sectional data.^8^

Among patients with NASH, data from a small short-term trial suggest that improvements in hepatic fibrosis and the NAFLD activity score are associated with increased HRQoL scores.^9^ However, it is unclear whether such relationship holds over longer time periods and whether worsening of disease activity is associated with reduced HRQoL scores. The aforementioned trial has also not adjusted changes in weight, which a potential significant confounder of such relationship, because it is associated with both changes in disease activity and changes in HRQoL.

The FLINT and PIVENS trials provide a good opportunity to investigate this relationship further given their rich dataset and primary analysis that showed no change in HRQoL between active treatment and placebo.^1 2^ These studies provide histological data from liver biopsies before and after the intervention compared with placebo arms, together with data on weight change and quality of life using the SF-36^10^ (a validated quality of life score, covering physical and mental components) at the start and end of the trials. The aim of the study is to investigate the association between disease activity and HRQoL scores in patients with NASH over 1.5 to 2 years. As the SF-36 contains information in different QoL domains, we can investigate specific QoL areas that may be impacted by disease activity.

# OBJECTIVES AND OUTCOME MEASURES

| **Objectives** | **Outcome Measures** |
| --- | --- |
| **Primary objectives**  To examine the association between changes in disease activity (fibrosis score) and changes in   1. Physical functioning 2. Physical role 3. Pain 4. General health 5. Fatigue 6. Social function 7. Emotional role 8. Emotional well-being | Univariable and multivariable regression coefficients between changes in disease activity (fibrosis score) and changes in   1. Physical functioning 2. Physical role 3. Pain 4. General health 5. Fatigue 6. Social function 7. Emotional role 8. Emotional well-being |
| **Secondary objectives**   1. Repeat the primary analysis with the NAFLD activity score as a measure of disease activity 2. To examine the association between changes in disease activity (fibrosis and the NAFLD activity score) and changes in 3. SF-36 physical component 4. SF-36 mental component | 1. Univariable and multivariable regression coefficients between changes in disease activity (as NAFLD activity score) and changes in 2. Physical functioning 3. Physical role 4. Pain 5. General health 6. Fatigue 7. Social function 8. Emotional role 9. Emotional well-being 10. Univariable and multivariable regression coefficients between changes in disease activity (fibrosis and the NAFLD activity score) and changes in 11. SF-36 physical component 12. SF-36 mental component |

# STUDY DESIGN

This is a secondary analysis of two previously published randomised controlled trials in adults with NASH: the Farnesoid X nuclear receptor ligand obeticholic acid for non-cirrhotic, non-alcoholic steatohepatitis (FLINT) ^1^ and the Pioglitazone versus Vitamin E versus Placebo for the Treatment of Nondiabetic Patients with Non-alcoholic Steatohepatitis (PIVENS) ^2^. This analysis employs a prospective longitudinal design.

# PARTICIPANT IDENTIFICATION

## Study Participants

Adults (18 years and over) with biopsy-proven NASH. This study will include data from all participants in the FLINT and PIVENS trials who have both a baseline and follow-up evaluable biopsy.

## Inclusion Criteria

- Adults with a biopsy-proven NASH.

## Exclusion Criteria

Standard exclusion criteria to trials in NASH applied in the FLINT and PIVENS trials as previously reported in the original publications ^1 2^.

# STATISTICS AND ANALYSIS

## Analysis of Outcome Measures

Data will be presented as mean (SD) or median (IQR) for continuous data and as percentages for categorical variables for the whole sample.

Correlation coefficients (Pearson’s or Spearman’s as appropriate) will be calculated to explore the univariable relationship between change in disease activity (separately for hepatic fibrosis and the NAFLD activity score) and changes in QoL scores (components of SF-36 as per section 4).

In the primary analysis, linear regression models will be used to explore the association between changes in hepatic fibrosis and changes in QoL scores (components of SF-36 as per section 4). Changes in fibrosis stage will be coded as “improved”, “stable”, “worsened”, if there is a change of >=-1, 0, >=+1 in the stage compared with baseline, respectively, as per the cut-offs for clinically meaningful disease changes in NASH clinical trials. Following univariable analysis, all models will be adjusted for sex (binary), age (continuous), baseline BMI (continuous), baseline fibrosis score (continuous), baseline value of the QoL dependent variable in the model (e.g., fatigue), trial (PIVENS or FLINT) and treatment (active vs. placebo), and weight change (continuous). We will also adjust for a dummy variable (able to take integer values 0-5) representing the number of specific co-morbidities (type II diabetes, GI disorder, MSK/ connective tissue disorders, nervous system disorders and psychiatric disorders)

In a secondary analysis, changes in disease activity will be defined as changes in the NAFLD activity score. This change will be coded as “improved”, “stable”, “worsened”, if there is a change of >=-2, -1–1, >=+2 in the stage compared with baseline, respectively, as per the cut-offs for clinically meaningful disease changes in NASH clinical trials. The multivariable models will be adjusted for the same covariates as the primary analysis with the exception of baseline NAFLD activity score instead of baseline fibrosis score. We will also investigate changes in cumulative totals of the physical (physical functioning, physical role, pain and general health) and mental (fatigue, social function, emotional role and emotional well-being) components of SF-36 with disease activity (both change in fibrosis stage and change in NAFLD activity score).

As SF-36 scores were taken at the same time as the liver biopsy, we anticipate minimal missing SF-36 data. In case of missing HRQoL data at follow-up, we will employ a last observation carried forward approach, since HRQoL was also measured in intermediate time points.

A recent secondary trial analysis (in progress) did not find any evidence of a moderating effect of weight change and change in fibrosis/ NAFLD disease activity score by treatment, trial, or baseline fibrosis score. Therefore, we are not planning to do such moderation analysis. The analysis found evidence of a moderating effect of trial arm (placebo vs. any active treatment) between weight change and NAFLD activity score. We will explore this relationship with the addition of an interaction term; trial arm*weight change.

Sensitivity analysis will be run

1. excluding participants with a diagnosis of no fibrosis at both baseline and end of treatment biopsy
2. complete case analysis (excluding participants with quality-of-life missing data at the biopsy follow up)

There will be no correction for multiple testing and significance will be set at p<0.05.

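### The cut-offs for 'improved' carry the wrong inequality sign (≥ −1 for fibrosis stage, ≥ −2 for NAFLD activity score), so the printed exposure categories overlap and leave out the largest improvers

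*Protocol*

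**What the plan says.** Section 7.1 of the Protocol (Analysis of Outcome Measures) states that in the primary analysis "linear regression models will be used to explore the association between changes in hepatic fibrosis and changes in QoL scores". Change in fibrosis stage enters as three categories, improved, stable and worsened, assigned "if there is a change of >=-1, 0, >=+1 in the stage compared with baseline, respectively". The secondary analysis uses the NAS with the same three labels, assigned "if there is a change of >=-2, -1–1, >=+2 in the stage compared with baseline, respectively". Both rules are justified in the same way: "as per the cut-offs for clinically meaningful disease changes in NASH clinical trials".

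No other part of the Protocol defines the categories. The Synopsis and section 4 refer only to changes in disease activity, so nothing elsewhere corrects or overrides the printed rule.

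**The concern.** On a signed scale, ≥ −1 means −1, 0, +1 and everything above. It does not mean a fall of 1 or more. The 'improved' category as printed therefore takes in everyone who was stable and everyone who worsened, and it excludes those who improved by 2 or more stages. The NAS rule has the same fault at −2.

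The rule defines the exposure in the primary models for eight SF-36 domains and in their NAS counterparts. The physical and mental component models use the same two disease measures and presumably the same coding. That makes 8 + 8 + (2 components × 2 measures) = 20 exposure–outcome pairs. The Protocol fixes this rule itself, so it is not a detail left to an analysis plan. Those with the greatest histological improvement matter most to the research question, and the printed rule gives them no category.

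**Working it through.** No sample size, power or significance figure is involved. The check is whether the three rules put every possible change into exactly one category.

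**Inputs, all from section 7.1.** Let c be the change from baseline, a whole number, with a negative value meaning improvement.

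- Fibrosis: improved c ≥ −1; stable c = 0; worsened c ≥ +1.
- NAS: improved c ≥ −2; stable −1 ≤ c ≤ +1; worsened c ≥ +2.

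The Protocol does not give the score ranges. Assumed maximum absolute change: 3 or 4 for fibrosis, 5 or 8 for NAS.

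**Step 1: the rules as printed.**

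| Measure | No category | Exactly one | Improved and stable | Improved and worsened |
|---|---|---|---|---|
| Fibrosis | c ≤ −2 | c = −1 | c = 0 | c ≥ +1 |
| NAS | c ≤ −3 | c = −2 | c = −1, 0, +1 | c ≥ +2 |

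Counts of possible values under each assumed range:

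| Measure, maximum change | Possible values | None | One | Two |
|---|---|---|---|---|
| Fibrosis, 3 | 7 | 2 | 1 | 4 |
| Fibrosis, 4 | 9 | 3 | 1 | 5 |
| NAS, 5 | 11 | 3 | 1 | 7 |
| NAS, 8 | 17 | 6 | 1 | 10 |

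The pattern does not depend on the range. These are counts of score values, not of participants.

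**Step 2: the sign of the 'improved' rule turned round.** With improved as c ≤ −1 (fibrosis) and c ≤ −2 (NAS), every whole-number change under each assumed range falls into exactly one category. There is no gap and no overlap.

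**Step 3: what literal programming would do.** Section 7.1 describes one variable with three levels. There are two ways of coding it in the printed order:

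- *First match wins.* Everyone with c ≥ −1 (NAS: c ≥ −2) becomes improved, stable and worsened are empty, and the rest are missing. With one level left, no contrast can be estimated.
- *Later lines overwrite earlier ones.* Improved shrinks to c = −1 exactly (NAS: c = −2 exactly). Stable and worsened come out right, but fibrosis changes of −2 or lower and NAS changes of −3 or lower are missing. The result looks like a valid three-level variable, and a regression that omits records with a missing exposure would leave out the largest improvers without comment.

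**The case against.** The strongest reply is that the intent is not in doubt. Three exclusive labels are matched in order to three values, stable is a fixed band around zero, and worsened mirrors improved with an explicit plus sign. Only one sensible partition fits: a fall of at least 1 stage, or of at least 2 NAS points. The printed form reads as shorthand for a change of at least that size in the negative direction. This stands, and it is why the point is minor. It does not make the text right, because the plus-signed entries in the same list are meant literally and the reversed sign appears twice with different numbers.

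A reader might infer that literal coding would remove or reverse the association. The Protocol does not support that. First-match coding gives no estimate at all and would be noticed at once. Overwriting leaves the remaining groups correctly classified and in the right order. Reversal would need something else, such as overlapping indicators entered together, which section 7.1 does not describe.

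Two further replies hold. The planned Pearson or Spearman correlations need not use the categories, so not every planned analysis depends on the rule. Missing exposure values could also be spotted in a simple tabulation, since section 6.1 includes only participants with both biopsies evaluable. That limits the risk of the overwriting route but relies on someone looking.

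Which level serves as reference, and the use of the word stage for the NAS, change no result and are not part of this point.

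**Conclusion.** The printed rule for 'improved' is wrong as written for both measures. Followed exactly, it double-classifies fibrosis changes of 0 or more and NAS changes of −1 or more. It leaves fibrosis changes of −2 or lower and NAS changes of −3 or lower unclassified.

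The severity is minor. The intended rule can be inferred, and the harm arises only if the text is programmed literally: either no estimable contrast, or loss of the largest improvers from the categorical models. The Protocol does not show that the analysis would be run that way. It gives no distribution of changes, so the number affected among the intended 422 participants cannot be stated.

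The conclusion assumes only that changes are whole numbers and that the printed signs mean what they say. It does not depend on the assumed score ranges.

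**What to change.** In section 7.1, state that change is the follow-up value minus the baseline value, and replace the two rules with:

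- Fibrosis stage: improved ≤ −1; stable 0; worsened ≥ +1.
- NAS: improved ≤ −2; stable −1 to +1; worsened ≥ +2.

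Wording such as a decrease of at least 1 stage, or of at least 2 points, would serve equally well. The cost is two inequality signs and one short sentence. The intended categories and models are unchanged, and there is no analytic downside.

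### The single active-versus-placebo term assumes, untested, that obeticholic acid, pioglitazone and vitamin E share one effect on each SF-36 domain; a five-level trial-arm factor would avoid this at little cost

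*Protocol*

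**What the plan says.** Protocol section 7.1 lists the covariates for the primary models, which relate change in fibrosis category to change in each of eight SF-36 domains. Among them are "trial (PIVENS or FLINT) and treatment (active vs. placebo), and weight change (continuous". The secondary models for NAFLD activity score use the same list, with the baseline score swapped.

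Section 5 identifies what lies behind the treatment term. One source trial is FLINT, which studied obeticholic acid. The other is PIVENS: "Pioglitazone versus Vitamin E versus Placebo for the Treatment of Nondiabetic Patients with Non-alcoholic Steatohepatitis". Active therefore covers three drugs, two of them in the same trial.

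Three other statements bear on the point:

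- Section 3 describes the source trials as having a "primary analysis that showed no change in HRQoL between active treatment and placebo". No figures by drug are given.
- Section 7.1 cites a separate analysis that "did not find any evidence of a moderating effect of weight change and change in fibrosis/ NAFLD disease activity score by treatment, trial, or baseline" (the last item being the fibrosis score at entry), and uses this to justify leaving out moderation analyses.
- Section 7.1 also reports a "moderating effect of trial arm (placebo vs. any active treatment) between weight change and NAFLD activity score", and plans to explore it with an interaction term.

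The two sensitivity analyses listed concern participants without fibrosis and participants with missing quality-of-life data. Neither separates the drugs.

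**The concern.** Change in histology is not randomised, so the coefficients of interest depend on what the model adjusts for. With one trial term and one binary treatment term, the active-minus-placebo difference on each domain is a single number for all three drugs. The trial term shifts the level of a whole trial, placebo arm included. It does not give obeticholic acid its own effect, and it cannot tell pioglitazone from vitamin E.

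The adjustment thus works at the level of active against placebo but not at the level of the drug. Suppose one drug produces more histological improvement than another and also moves quality of life by a route other than histology or weight. Part of that second effect would then appear in the coefficient for improved or worsened disease. The same coding is used for all eight primary domains and again in the secondary models, each tested at p<0.05 without correction for multiplicity.

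Nothing in the Protocol supports a common drug effect. The cited absence of moderation concerns the relation between weight change and histology, not drug effects on quality of life.

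**Working it through.** The Protocol gives no figure to reproduce: 422 participants are stated (section 1) without an effect size, standard deviation or split by arm. The check is a large-sample least-squares calculation of the bias when the true association between histology and quality of life is zero.

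**Inputs from the Protocol.** N = 422; five trial-by-arm groups; planned adjustment by trial plus active/placebo.

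**Inputs assumed.**
- Group sizes: 100 in each FLINT arm and 74 in each PIVENS arm (total 422).
- Probability of improvement: 0.25 on placebo, 0.40 on obeticholic acid, and 0.40 on average for the two PIVENS drugs, which differ by 10 points (0.45/0.35) or 20 points (0.50/0.30).
- Direct effect on quality of life: +g/2 for one PIVENS drug and −g/2 for the other, with g = 2, 5 or 10 points; zero in the other arms.
- SD of quality-of-life change: 15, 20 or 25 points.
- Simplification: improved versus not improved, without the other covariates.

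**Formula.** Let r be each group's improvement probability minus the value fitted from trial and active/placebo.

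Bias = Σ n·r·(direct effect) / [Σ n·p(1−p) + Σ n·r²]

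**Example, 20-point difference and g = 5.** Here r is +0.10 and −0.10 in the two PIVENS drug groups and 0 elsewhere.
- Numerator: 74 × (0.10 × 2.5 + 0.10 × 2.5) = 37.0
- Within-group sum: 100(0.1875 + 0.24) + 74(0.1875 + 0.25 + 0.21) = 90.665
- Between-group sum: 74 × (0.01 + 0.01) = 1.48
- Bias = 37.0 / 92.145 = 0.40 points

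**Results (points on the improved coefficient).**

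| Difference in improvement | g = 2 | g = 5 | g = 10 |
|---|---|---|---|
| 10 points | 0.08 | 0.20 | 0.40 |
| 20 points | 0.16 | 0.40 | 0.80 |

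The bias is zero if either difference is zero. A second assumed split (FLINT placebo 17%, obeticholic acid 24%, PIVENS placebo 18%, pioglitazone 18%, vitamin E 23%) gives 0.09 to 0.92 over the same grid. Stretching the improvement difference to 30 points (0.60/0.30) with g = 10 gives 1.19 with the first group sizes. Reversing which drug is worse for quality of life reverses the sign throughout. With a five-level factor, r is zero in every group and so is the bias.

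**Scale.** The standard error of the same coefficient is SD/√92.145 = SD/9.60, which is 1.56, 2.08 and 2.60 for SD 15, 20 and 25. A simple two-group formula with 36% improved gives 1.52, 2.03 and 2.54. A bias of 0.9 against a standard error of 1.56 to 2.60 is 0.35 to 0.58 standard errors, which would raise the false-positive rate of one 5% test to about 6% to 9%.

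**Cost of the five-level factor.** The planned model has 12 parameters: intercept, two disease-change categories, sex, age, BMI, baseline fibrosis, baseline domain score, trial, treatment, weight change and comorbidity count. That leaves 410 residual degrees of freedom; the five-level factor leaves 408.
- Degrees of freedom alone: √(410/408) = 1.002
- Correlation of arm with improvement, 10-point difference: √(92.145/91.775) = 1.002
- The same, 20-point difference: √(92.145/90.665) = 1.008

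Multiplied together, the standard error rises by about 0.5% to 1.1%. Other scenarios with a 20-point difference reach about 1.2%.

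**The case against.** The strongest reply is that the harm is conditional and nothing in the Protocol shows that the condition is met. The drugs must differ in histological response and also in a quality-of-life effect that bypasses both histology and weight. Weight change is already a covariate, so a drug effect acting through weight is largely absorbed. The only statement on drugs and quality of life, in section 3, is that active treatment and placebo did not differ. A 10-point gap between the two PIVENS drugs with histology and weight held fixed is close to a worst case; at 2 points the bias is only about 0.1 to 0.2.

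Most of this stands, and it limits the point. A reader might infer that the planned coding does leave drug-level confounding in the results, for instance through tolerability. The documents do not support that: they give no arm-level histology or quality-of-life data and say nothing on tolerability. Nor can the direction of any bias be stated. What does not follow is that a common effect has been established. A null result for active against placebo, given without figures by drug, does not exclude opposing drug effects or show equality in eight domains.

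A reader might also take the pooled contrast in the planned interaction between trial arm and weight change for the same fault. It is not an error there: the interaction is motivated by a result, cited in section 7.1, that is expressed in that same contrast.

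**Conclusion.** The primary and secondary multivariable models rest on an unstated and untested assumption that three drugs share one effect on each SF-36 domain. Residual confounding is possible, not demonstrated. Over the assumed range it amounts to about 0.1 to 0.9 SF-36 points of either sign, below one standard error (about 1.5 to 2.6 points), and to nothing if the drugs differ on only one of the two paths. These sizes depend wholly on assumed group sizes, improvement rates, direct effects and SDs. The point does not threaten the study. It is still worth acting on, because any such bias would not shrink with sample size, no planned sensitivity analysis would reveal it, and the restriction can be lifted almost for free.

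**What to change.** In section 7.1, replace the separate trial and treatment covariates in all multivariable models with one five-level factor: FLINT obeticholic acid, FLINT placebo, PIVENS pioglitazone, PIVENS vitamin E, PIVENS placebo. The planned model is a special case of this one, so no adjustment is lost and the common-effect assumption can be tested directly.

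The cost is a line of text, two extra degrees of freedom and a standard error larger by about 0.5% to 1.2% under the assumed inputs. It needs only the assigned arm from the source trials. The exploratory interaction between trial arm and weight change may keep its contrast of placebo with any active treatment; a five-level version would use four interaction terms instead of one and is not needed for its stated purpose.

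### The adjusted NAFLD activity score (NAS) models drop baseline fibrosis without a stated reason; keeping it beside baseline NAS is a cheap guard against plausible, unproven confounding

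*Protocol*

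**What the plan says.** Section 7.1 (Analysis of Outcome Measures) lists the adjustment set for the primary fibrosis models. It includes "baseline BMI (continuous), baseline fibrosis score (continuous), baseline value of the QoL dependent variable in the model", together with sex, age, trial, treatment, weight change and a count of co-morbidities. Baseline NAS is not on the list.

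The NAS models come next: "In a secondary analysis, changes in disease activity will be defined as changes in the NAFLD activity score". They take over the primary covariates "with the exception of baseline NAFLD activity score instead of baseline fibrosis score". Each adjusted model therefore carries the baseline of its own exposure and not the baseline of the other.

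The same section also plans unadjusted correlations between "change in disease activity (separately for hepatic fibrosis and the NAFLD activity score) and changes in QoL scores", and section 4 lists univariable as well as multivariable coefficients. For the physical and mental totals of the SF-36, section 7.1 names the two disease measures but does not repeat the covariates.

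The Background (section 3) says that patients with NASH-related cirrhosis "have poorer HRQoL scores than those with non-cirrhotic NASH", and describes hepatic fibrosis as a feature "which is the strongest predictor for long-term liver morbidity and mortality".

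**The concern.** The analysis estimates an observational association between two changes, so it depends on adjusting for common causes. Baseline fibrosis is measured before either change. It is available for everyone, because section 6.1 requires evaluable biopsies at baseline and follow-up, and it is already in the primary models. The protocol's own Background ties it to QoL. If it also relates to how NAS moves during follow-up, leaving it out biases the adjusted NAS coefficients.

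Adjusting for baseline QoL closes part of this path. It removes the fibrosis-related difference in starting level, but not necessarily any fibrosis-related difference in later change.

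At stake are the multivariable NAS models for the eight SF-36 domains and, if they use the same list, those for the two totals. Fibrosis and NAS results will probably be read side by side, and some of any difference between them could then come from the covariates rather than from the disease measure.

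**Working it through.** The plan has no figure of its own to reproduce: 422 is an intended number without a derivation, and no effect size is given. The check therefore asks what the omission could cost and what the remedy costs.

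**Inputs from the protocol**
- N = 422 (Synopsis).
- Significance at p<0.05 without multiplicity correction (section 7.1), taken here as two-sided.
- Terms in an adjusted NAS model (section 7.1): two indicators for the three-category NAS change, plus sex, age, baseline BMI, baseline NAS, baseline QoL, trial, treatment, weight change and co-morbidity count. That is 2 + 9 = 11, without the arm-by-weight-change interaction.

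**Inputs not in the protocol (assumed)**
- r: partial correlation of baseline fibrosis with NAS change, given the other covariates.
- b: standardised effect of baseline fibrosis on QoL change, given the same covariates.

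**Degrees of freedom.** 422 − 11 − 1 = 410 residual degrees of freedom as planned, and 409 with baseline fibrosis added.

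**Bias from the omission.** Treat NAS change as one continuous standardised exposure, a simplification of the three categories:
- bias ≈ b × r
- SE ≈ 1/√410 = 0.0494
- δ = bias/SE
- rejection rate of a nominal 5% test when there is no true association = 1 − Φ(1.96 − δ) + Φ(−1.96 − δ)

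| r | b | Bias (SD) | Bias in SE | Rejection rate |
|---|---|---|---|---|
| 0 | any | 0 | 0 | 5.0% |
| 0.1 | 0.05 | 0.005 | 0.10 | 5.1% |
| 0.1 | 0.1 | 0.010 | 0.20 | 5.5% |
| 0.2 | 0.1 | 0.020 | 0.40 | 6.9% |
| 0.2 | 0.2 | 0.040 | 0.81 | 12.8% |
| 0.3 | 0.2 | 0.060 | 1.21 | 22.9% |

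The last row shows how quickly the product grows. Nothing in the protocol points to values that large, and the range carried forward is 0.1 to 0.8 SE.

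**Cost of the remedy.** The SE of the NAS-change coefficient rises by a factor 1/√(1 − r²), before any gain from a smaller residual variance:
- r = 0.1: 1/√0.99 = 1.005, a rise of 0.5%
- r = 0.3: 1/√0.91 = 1.048, a rise of 4.8%

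The two sides move together. If r is near zero there is no bias and practically no cost; if r is larger the protection matters more and the price is still small.

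**The case against.** The strongest defence is that the swap is a coherent, symmetric choice: each model is adjusted for the baseline of its own exposure, everything else is shared, and nothing is contradicted. That stands. This is a possible improvement, not an error.

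The second defence is that confounding is not shown. The Background calls weight change a potential confounder because it relates both to the change in disease activity and to the change in QoL. For baseline fibrosis the protocol documents neither link. The cirrhosis statement is about QoL level, baseline QoL is already in the model, and FLINT by its title enrolled non-cirrhotic disease. The statement on long-term morbidity and mortality concerns neither QoL change nor NAS change. This also stands, and it limits the claim to plausibility. It does not remove the reason to adjust: by the Background's own wording, a potential confounder was enough to fault an earlier trial for not adjusting for weight change.

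The earlier secondary analysis mentioned in section 7.1 found no moderation by baseline fibrosis. That concerns effect modification and neither supports nor excludes confounding. The planned sensitivity analysis excluding people without fibrosis at both biopsies does not adjust for baseline stage among those who remain.

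A reader might infer that every NAS analysis is affected. That is too wide, because the univariable analyses are unadjusted by design. A reader might also infer that the eight primary fibrosis models are defective for lacking baseline NAS. The protocol offers no evidence that baseline NAS confounds them, so it does not support requiring that change. Nor does it plan a formal comparison of the two disease measures, which weakens the argument from unequal adjustment sets.

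**Conclusion.** The point holds as a minor one, limited to the multivariable NAS models, which are secondary. Baseline fibrosis is removed from them without a stated reason although it is available, precedes both changes and is a plausible common cause.

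The possible bias runs from negligible (about 0.1 SE, 5.1% rejection) to moderate (about 0.8 SE, about 13%). This rests wholly on assumed associations: r = 0.1 with b = 0.05 at the low end, 0.2 for both at the high end. It also treats NAS change as a single continuous exposure and assumes that all 422 participants contribute. If baseline fibrosis is unrelated to NAS change given the other covariates, there is no bias at all. One should not conclude that the NAS results will be biased; the document does not establish it. The case for the change is that it costs almost nothing compared with what it might prevent.

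**What to change.** In section 7.1, replace the sentence on the NAS covariates with, for example: *The adjusted NAS models will use the full covariate list of the primary models, with baseline fibrosis score retained, and will add the baseline NAFLD activity score.* The same sentence could say whether this list also governs the models for the physical and mental totals. If the sponsor prefers the swap, a one-line justification or a sensitivity analysis with both baseline scores would also answer the point.

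Adding baseline NAS to the primary fibrosis models is optional, for instance as a sensitivity analysis, and the main point does not depend on it.

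Cost: one sentence, one degree of freedom per NAS model (410 to 409), an SE increase of about 0.5% to 5% over the assumed range, and no new data.
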